**Table 1: Dose modifications**

### ***Dose modifications for use with potent CYP3A inhibitors***

Concomitant use of potent CYP3A inhibitors (see section 5.5 below) should be avoided, and alternative concomitant medication with no or minimal CYP3A inhibition should be considered. If coadministration of IBRANCE with a potent CYP3A inhibitor cannot be avoided, reduce the dose of IBRANCE to 75 mg per day. When the potent inhibitor is discontinued, increase the dose of IBRANCE (after 3-5 inhibitor half-lives) to the dose used prior to initiation of the potent CYP3A inhibitor.

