### Cohort 2 (second phase) – Chordomas

- 1) Previous treatment with any anti-CDK4 or immune checkpoint inhibitors.
- 2) Diagnosis other than chordoma at central review.
- 3) Patients irradiated in the only available target lesion.
- 4) Patients who have received more than three lines for advanced disease.
- 5) History of other neoplastic disease except for adequately treated basal cell carcinoma or cervical cancer in situ. This criterion will be assessed individually with the research team.
- 6) Severe cardiovascular disease (NYHA  $\geq$  2).
- 7) Toxicity grade 3 or higher according to CTCAE 5.0 if, in the opinion of the investigator, it may significantly interfere with the toxicity of the drug under study.
- 8) Patients who have not recovered from previous toxicity up to CTCAE grade 1 due to previous antineoplastic treatment with chemotherapy, radiotherapy, or biological therapy (including monoclonal antibodies).
- 9) Patients who have not recovered from minor or major surgery or who have had major surgery in the 4 weeks prior to the start of study treatment.
- 10) Metastasis in the central nervous system.
- 11) Patients who are pregnant or breastfeeding, or who expect to conceive children during the treatment period.

- 12) Foods or drugs known to be CYP3A4 inhibitors/inducers; CYP3A4 substrates with narrow therapeutic ranges or known to prolong the QTc interval.
- 13) Major surgery, chemotherapy, radiotherapy, any investigational agent, or other antineoplastic therapy within 4 weeks prior to inclusion. Patients who have received previous radiotherapy  $\geq 25\%$  of bone marrow are ineligible, regardless of when it was received.
- 14) QTc > 480 ms; personal or family history of long or short QT syndrome, Brugada syndrome or known history of QTc prolongation, or Torsades de Pointes (TdP).
- 15) Any of the following situations within 6 months prior to study drug administration: myocardial infarction, severe/unstable angina, current cardiac dysrhythmias of Grade  $\geq 2$  NCI-CTCAE version 5.0, atrial fibrillation of any grade, coronary/peripheral artery pacemaker implantation, symptomatic congestive heart failure, cerebrovascular accident including transient ischemic attack, symptomatic pulmonary embolism, or severe interstitial lung disease (ILD)/pneumonitis.
- 16) Known hypersensitivity to any PD 0332991 or excipients.
- 17) Active or recent suicidal intent or behavior.

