### 5.2 Interruptions and dose modifications

Management of some adverse events may require temporary dose interruptions or delays and/or dose reductions, or permanent discontinuation. Recommended dose modifications of IBRANCE are based on individual safety and tolerability.

Complete blood counts should be monitored prior to initiation of IBRANCE treatment and at the beginning of each cycle, as well as on day 14 of the first two cycles, as clinically indicated.

| Recommended dose modifications for adverse events |             |
|---------------------------------------------------|-------------|
| Dose level                                 | Dose |
| Recommended initial dose                          | 125 mg/day  |
| First dose reduction                              | 100 mg/day  |
| Second dose reduction                             | 75 mg/day*  |

\*If a dose reduction below 75 mg/day is required, treatment should be discontinued.

Dose modification instructions for hematologic and non-hematologic toxicities are detailed below:

| Hematologic toxicities                                                                                                         |                                                                                                                                                                                                                                                                                                                                                                                                                                                                                                 |
|--------------------------------------------------------------------------------------------------------------------------------|-------------------------------------------------------------------------------------------------------------------------------------------------------------------------------------------------------------------------------------------------------------------------------------------------------------------------------------------------------------------------------------------------------------------------------------------------------------------------------------------------|

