### ***Effect of CYP3A inhibitors***

Coadministration of a potent CYP3A inhibitor (itraconazole) increased the plasma exposure of palbociclib in healthy subjects by 87%. Avoid concomitant use of CYP3A inhibitors (e.g., clarithromycin, indinavir, itraconazole, ketoconazole, lopinavir/ritonavir, nefazodone, nelfinavir, posaconazole, ritonavir, saquinavir, telaprevir, telithromycin, verapamil, and voriconazole). Grapefruit or grapefruit juice should be avoided during treatment with IBRANCE. If coadministration of IBRANCE with a potent CYP3A inhibitor cannot be avoided, reduce the dose of IBRANCE.

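### The flat 75 mg/day rule for unavoidable potent CYP3A inhibitors gives no workable instruction for a patient already at 75 mg/day, and by the protocol's own figure leaves patients reduced for toxicity above starting-dose exposure

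*Protocol*

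**What the plan says.** Section 5.2 of the Protocol has a dose-level table for adverse events with three steps: 125 mg/day ("Recommended initial dose"), 100 mg/day after a first reduction and 75 mg/day after a second. Its footnote adds: "If a dose reduction below 75 mg/day is required, treatment should be discontinued".

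A separate subsection of 5.2 covers potent CYP3A inhibitors. They are to be avoided, but: "If coadministration of IBRANCE with a potent CYP3A inhibitor cannot be avoided, reduce the dose of IBRANCE to 75 mg per day". The target is not tied to the dose the patient is taking. Once the inhibitor has stopped and a washout has passed, the dose goes back up "to the dose used prior to initiation of the potent CYP3A inhibitor".

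Section 5.4, on CYP3A inhibitors, addresses the same situation without a target: "If coadministration of IBRANCE with a potent CYP3A inhibitor cannot be avoided, reduce the dose of IBRANCE". The same paragraph gives the size of the interaction: "Coadministration of a potent CYP3A inhibitor (itraconazole) increased the plasma exposure of palbociclib in healthy subjects by 87" per cent.

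For the inhibitors concerned, the 5.2 subsection sends the reader to section 5.5. That section is about pregnancy and lactation; the list of drugs is in 5.4.

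**The concern.** A rule that names one absolute dose works only if every patient to whom it applies is above that dose. Here 75 mg/day is also the lowest level of the toxicity ladder, so a patient can already be there when an inhibitor becomes unavoidable. The rule then changes nothing for someone who has needed two reductions for toxicity, while the drug's exposure rises. A patient at 100 mg/day does get a cut, but it may be too small to offset the interaction.

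What is at stake is patient safety and uniform handling across sites. A site that follows 5.2 to the letter raises exposure in a patient who has shown intolerance. A site that starts from 5.4 finds an instruction to reduce that no defined dose level can satisfy, with the discontinuation footnote beside it.

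**Working it through.** The protocol does not derive the 75 mg figure, so there is no plan calculation to reproduce. The check has two parts.

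**1. The three texts for a patient at 75 mg/day**

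- Section 5.2, inhibitor subsection: the target is 75 mg/day, so the dose does not change.
- Section 5.4: the dose is to be reduced, by an unstated amount. The table has no level below 75 mg/day.
- Section 5.2, table footnote: treatment stops if a reduction below 75 mg/day is required. Nothing says whether the instruction in 5.4 counts as requiring one.

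No other text in the protocol settles the case.

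**2. Exposure under the flat rule**

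Inputs from the protocol: dose levels 125, 100 and 75 mg/day (5.2 table); dose with an inhibitor 75 mg/day (5.2 subsection); exposure increase 87%, a factor of 1.87 (5.4).

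Assumptions that are not in the protocol: exposure is proportional to dose, and the itraconazole result in healthy subjects carries over to trial patients and to other potent inhibitors.

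- Equivalent dose without inhibitor = 75 × 1.87 = 140.25 mg.
- Nominal cut = 1 − 75 / prior dose.
- Exposure relative to the patient's own prior level = 140.25 / prior dose.
- Exposure relative to the full starting dose = 140.25 / 125 = 1.12, whatever the prior dose.

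| Prior dose (mg/day) | Nominal cut | Exposure vs own prior level |
|---|---|---|
| 125 | 40% | 140.25 / 125 = 1.12 |
| 100 | 25% | 140.25 / 100 = 1.40 |
| 75 | 0% | 140.25 / 75 = 1.87 |

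**Sensitivity to the 87% figure.** The flat dose fully offsets the interaction when the exposure factor is no more than prior dose / 75:

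- from 125 mg: 125 / 75 = 1.67
- from 100 mg: 100 / 75 = 1.33
- from 75 mg: 75 / 75 = 1.00

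So a weaker interaction of +33% leaves the patient from 100 mg level (1.00) and the patient from 75 mg at 1.33 times prior exposure. At +67% those ratios are 1.25 and 1.67, and both patients reach the exposure of the full starting dose (75 × 1.67 = 125). For the patient already at 75 mg, any increase passes through in full.

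**The case against.** The best defence is that the case is uncommon and the rule sound where it will mostly be used. It takes a patient who has been reduced for toxicity and also needs a potent inhibitor that both sections say to avoid. From 125 mg the rule brings exposure to about 1.12 times the prior level, broadly in line with the 87% figure. The modifications are described as recommendations based on individual tolerability, and section 4.3 lets the investigator stop treatment for unacceptable risk. All of that stands. It makes the case rarer and leaves room for judgement, but does not say what the protocol asks for at 75 mg/day.

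Several stronger readings are tempting, and the documents do not support them:

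- *Every patient reduced for toxicity gets no reduction.* False at 100 mg/day, where the cut is 25%.
- *The rule conflicts with the dose-level table as a whole.* The table covers adverse events, and 75 mg is one of its levels, not below its floor.
- *One text continues treatment and the others order it stopped.* Section 5.4 never says stop, and the footnote is conditional. Discontinuation is a possible reading when the two are combined, not an explicit order.
- *The return rule collides with toxicity reductions.* It goes back to the pre-inhibitor dose and so keeps reductions made before the inhibitor. A patient who has been discontinued has no dose to return to.
- *The exclusion criteria contradict the on-study rule.* Section 4.2 lists "Foods or drugs known to be CYP3A4 inhibitors/inducers" as a bar to entry; 5.2 and 5.4 deal with a need that arises later. Entry and on-study rules may differ.
- *The 6-month PFS result would depend on which sentence a site reads.* The protocol gives no basis for sizing such an effect.

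The exposure ratios also rest on two assumptions that the protocol does not state. That is fair, and the sensitivity check shows which statements depend on the size of the interaction.

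**Conclusion.** The point holds for patients already below 125 mg/day. At 75 mg/day the inhibitor rule is no reduction, and the three texts cannot be followed together; this does not depend on any pharmacological assumption. At 100 mg/day the texts can be followed, but the 25% cut does not offset an 87% increase.

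Under dose proportionality and carry-over of the itraconazole figure, prior exposure is multiplied by about 1.40 from 100 mg and 1.87 from 75 mg. Both groups end about 12% above the exposure of the full starting dose, so the rule undoes reductions made for toxicity. That last statement needs an interaction of more than about 67%.

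There is no defect of this kind at 125 mg/day. The wrong cross-reference is a plain error. The list in 5.4 is a smaller matter: the sentence that introduces it does not say potent, although the sentences around it and the paragraph on inducers do, so it is unclear which listed drugs trigger the dose change.

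**What to change.** The sponsor should:

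- reconcile the dose-level footnote in 5.2, the inhibitor subsection in 5.2 and the inhibitor paragraph in 5.4, so that a patient at 100 mg/day and a patient at 75 mg/day each have one unambiguous instruction;
- state whether the 75 mg floor applies when the patient reached 75 mg/day only because of an inhibitor;
- change the pointer in the 5.2 subsection from section 5.5 to section 5.4;
- mark which drugs listed in 5.4 count as potent inhibitors for this rule.

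Which dose or stopping rule applies in each case is a clinical decision for the sponsor; this review does not propose one. The cost is a wording amendment and a letter to sites, with no extra patients, visits or procedures.

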### **5.3 Treatment overdose**

In the event of an overdose (defined as an administration greater than the dose specified in the protocol), investigators should contact the CRO assigned by the Sponsor, and additional monitoring of the patient's adverse events and laboratory abnormalities should be considered. Decisions regarding dose interruptions or modifications will be discussed by the investigator and the Sponsor's coordinating investigator based on the clinical evaluation of the patient. Information related to the amount of excess dose should be documented in the eCRF.

There is no known antidote for IBRANCE. Treatment of an overdose of IBRANCE should consist of general supportive measures.

### **5.4 Concomitant medication**

All patients will be asked to provide a complete list of prescriptions and medications taken during the 4 weeks prior to the start of screening. Investigators should be informed, as soon as possible, of any medications taken from the start of screening until the first post-treatment follow-up visit.

All concomitant medications taken during the study will be recorded in the eCRF, including indication, dosing information, and dates of administration. If future changes are made to the list of permitted/prohibited medications, formal documentation will be provided and kept in the investigator's file. Such changes will be communicated to the research centers in the form of a letter.

### ***Effect of CYP3A inhibitors***

Coadministration of a potent CYP3A inhibitor (itraconazole) increased the plasma exposure of palbociclib in healthy subjects by 87%. Avoid concomitant use of CYP3A inhibitors (e.g., clarithromycin, indinavir, itraconazole, ketoconazole, lopinavir/ritonavir, nefazodone, nelfinavir, posaconazole, ritonavir, saquinavir, telaprevir, telithromycin, verapamil, and voriconazole). Grapefruit or grapefruit juice should be avoided during treatment with IBRANCE. If coadministration of IBRANCE with a potent CYP3A inhibitor cannot be avoided, reduce the dose of IBRANCE.

### **Effect of CYP3A inducers**

Coadministration of a potent CYP3A inducer (rifampicin) reduced the plasma exposure of palbociclib in healthy patients by 85%. Avoid concomitant use of potent CYP3A inducers (e.g., phenytoin, rifampicin, carbamazepine, and St. John's wort).

### **5.5 Pregnancy and lactation**

Due to its mechanism of action, IBRANCE may cause fetal harm. Women of reproductive potential (and their partners) should use effective contraceptive measures throughout therapy with IBRANCE, and for at least 90 days after the last dose. Women should contact their physician if they become pregnant or if pregnancy is suspected during treatment with IBRANCE. Women should not breastfeed while being treated with IBRANCE because of the potential for serious adverse reactions in infants.

## 6. MEDICATION MANAGEMENT

### 6.1 Pharmaceutical form of palbociclib

IBRANCE 125 mg hard capsules: hard, opaque capsule with a caramel-colored body (with “PBC 125” printed in white) and a caramel-colored cap (with “Pfizer” printed in white). The capsule length is  $21.7 \pm 0.3$  mm.

IBRANCE 100 mg hard capsules: hard, opaque capsule with a light orange body (with “PBC 100” printed in white) and a caramel-colored cap (with “Pfizer” printed in white). The capsule length is  $19.4 \pm 0.3$  mm.

IBRANCE 75 mg hard capsules: hard, opaque capsule with a light orange body (with “PBC 75” printed in white) and a light orange cap (with “Pfizer” printed in white). The capsule length is  $18.0 \pm 0.3$  mm.

### 6.2 Supply of study medication

Palbociclib (IBRANCE) is a drug developed and marketed by Pfizer. In the GEIS-51 trial, palbociclib will be supplied by Pfizer through the distribution company Alcura Health España, S.A.

### 6.3 Packaging, labelling and distribution

The contents of the investigational product label will meet the requirements of the applicable regulations in Spain. The study drug will be labelled and distributed directly to the pharmacy services of each participating center by the distribution company Alcura Health España, S.A., in coordination with the study CRO.

### 6.4 Storage in local pharmacies

Palbociclib should be stored in local pharmacies in a secure area under physical conditions appropriate for the product (palbociclib does not require special storage conditions). Access to and administration of the medication should be limited to authorized personnel of the center.

### 6.5 Dispensation to patients

The study drug should be dispensed by local pharmacies only to enrolled patients and according to protocol guidelines.

### 6.6 Drug accountability

In compliance with local regulatory requirements, designated site personnel should document the amount of medication received by the pharmacy from the Sponsor, the amount dispensed to trial patients, and the amount returned by patients to the pharmacy. Drug accountability documentation should be kept up to date throughout the course of the trial and will be filed according to the applicable regulations.

### 6.7 Treatment adherence

A record of the quantities of palbociclib dispensed and returned by each patient should be maintained and reconciled with the eCRF. During the course of the study and after its completion, all unused or expired trial medication will be accounted for and destroyed at the site.

### 6.8 Responsibilities of local pharmacies

The responsibilities of the designated responsible pharmacist at each participating site include, but are not limited to, ensuring that:

- The study drug is handled and stored safely and according to product-specific requirements;
- The study drug is dispensed only to trial patients according to protocol;
- There is a sufficient supply of the study drug for the treatment of patients, with timely notification to the Sponsor so that medication refills can be made;
- Study drug expiration dates are monitored, and that medication is used in order of expiration date (first to expire, first);
- Unused or expired medication is destroyed according to the local procedure at each site;
- Records of receipt, accounting and destruction of study medication are maintained.

## 7. PROCEDURES AND EVALUATIONS

### 7.1 Schedule of activities

| Protocol section | Stages >>                                  | PRE-TREAT.                                                    | TREATMENT                                                                        |        |       |                                                    |       |       |       |       |       |       |       |                        | END TREAT. 
(+/- 7 days) | FOLLOW-UP
(+/- 7 days)  |
|------------------|--------------------------------------------|---------------------------------------------------------------|----------------------------------------------------------------------------------|--------|-------|----------------------------------------------------|-------|-------|-------|-------|-------|-------|-------|------------------------|-----------------------------------------|----------------------------|
|                  |                                            | Screening 
(≤ 28 days from start of treatment) | C1 D1                                                                            | C1 D14 | C2 D1 | C2 D14                                             | C3 D1 | C4 D1 | C5 D1 | C6 D1 | C7 D1 | C8 D1 | C9 D1 | C10 D1
...
Cn D1 |                                         |                            |
| 7.2              | Patient information and consent            |                                                               |                                                                                  |        |       |                                                    |       |       |       |       |       |       |       |                        |                                         |                            |
|                  | Information to the patient                 | X (before screening)                                          |                                                                                  |        |       |                                                    |       |       |       |       |       |       |       |                        |                                         |                            |
|                  | Informed consent                           | X (before screening)                                          |                                                                                  |        |       |                                                    |       |       |       |       |       |       |       |                        |                                         |                            |
| 7.3              | Eligibility and inclusion procedures       |                                                               |                                                                                  |        |       |                                                    |       |       |       |       |       |       |       |                        |                                         |                            |
|                  | CDK4 overexpression analysis               | X                                                             |                                                                                  |        |       |                                                    |       |       |       |       |       |       |       |                        |                                         |                            |
|                  | Eligibility confirmation                   | X                                                             |                                                                                  |        |       |                                                    |       |       |       |       |       |       |       |                        |                                         |                            |
|                  | Patient recruitment                        | X                                                             |                                                                                  |        |       |                                                    |       |       |       |       |       |       |       |                        |                                         |                            |
| 7.4              | Clinical evaluations                       |                                                               |                                                                                  |        |       |                                                    |       |       |       |       |       |       |       |                        |                                         |                            |
|                  | Demographics and medical history           | X                                                             |                                                                                  |        |       |                                                    |       |       |       |       |       |       |       |                        |                                         |                            |
|                  | ECOG                                       | X                                                             | X                                                                                | X      | X     | X                                                  | X     | X     | X     | X     | X     | X     | X     | X                      | X                                       |                            |
| 7.5              | Laboratory tests  (+/- 3 days) |                                                               |                                                                                  |        |       |                                                    |       |       |       |       |       |       |       |                        |                                         |                            |
|                  | Biochemistry                   | X                                                             | X                                                                                | X      | X     | X                                                  | X     | X     | X     | X     | X     | X     | X     | X                      | X                                       |                            |
|                  | Hematology                     | X                                                             | X                                                                                | X      | X     | X                                                  | X     | X     | X     | X     | X     | X     | X     | X                      | X                                       |                            |
|                  | Coagulation tests                          | X                                                             |                                                                                  |        |       |                                                    |       |       |       |       |       |       |       |                        |                                         |                            |
|                  | Pregnancy test                 | X                                                             |                                                                                  |        |       |                                                    | X     |       |       |       | X     |       |       | X          |                                         |                            |
| 7.6              | Safety evaluations                         |                                                               |                                                                                  |        |       |                                                    |       |       |       |       |       |       |       |                        |                                         |                            |
|                  | Physical examination           | X                                                             | X                                                                                | X      | X     | X                                                  | X     | X     | X     | X     | X     | X     | X     | X                      | X                                       |                            |
|                  | Vital signs                                | X                                                             | X                                                                                | X      | X     | X                                                  | X     | X     | X     | X     | X     | X     | X     | X                      | X                                       |                            |
|                  | Adverse events                             |                                                               | Throughout the course of treatment                                               |        |       |                                                    |       |       |       |       |       |       |       |                        |                                         |                            |
|                  | Concomitant medication                     | X                                                             | Throughout the course of treatment                                               |        |       |                                                    |       |       |       |       |       |       |       |                        |                                         |                            |
|                  | ECG                            | X                                                             |                                                                                  |        |       |                                                    |       |       |       |       |       |       |       |                        |                                         |                            |
|                  | LVEF                                       | X                                                             |                                                                                  |        |       |                                                    |       |       |       |       |       |       |       |                        | X                                       |                            |
| 7.7              | Efficacy evaluations                       |                                                               |                                                                                  |        |       |                                                    |       |       |       |       |       |       |       |                        |                                         |                            |
|                  | Radiological evaluation        | X                                                             | Every 8 weeks (irrespective of cycle delays)                                     |        |       |                                                    |       |       |       |       |       |       |       |                        | X                                       |                            |
|                  | Additional imaging tests      | X                                                             | Every 8 weeks                                                                    |        |       |                                                    |       |       |       |       |       |       |       |                        |                                         |                            |
|                  | Central radiological review                |                                                               |                                                                                  |        |       |                                                    |       |       |       |       |       |       |       |                        | X                                       |                            |
| 7.8              | Treatment control                          |                                                               |                                                                                  |        |       |                                                    |       |       |       |       |       |       |       |                        |                                         |                            |
|                  | Medication dispensing         |                                                               | X                                                                                |        | X     |                                                    | X     | X     | X     | X     | X     | X     | X     | X                      |                                         |                            |
|                  | Intake of medication                       |                                                               | Palbociclib 125 mg once daily for 3 weeks followed by 1 week off (28-day cycles) |        |       |                                                    |       |       |       |       |       |       |       |                        |                                         |                            |
|                  | Treatment adherence                        |                                                               | Every 4 weeks                                                                    |        |       |                                                    |       |       |       |       |       |       |       |                        |                                         |                            |
| 7.9              | Collection of biological samples           |                                                               |                                                                                  |        |       |                                                    |       |       |       |       |       |       |       |                        |                                         |                            |
|                  | Tumor block collection        | X                                                             |                                                                                  |        |       |                                                    |       |       |       |       |       |       |       |                        |                                         |                            |
|                  | Blood collection              | X                                                             |                                                                                  |        | X     | Every 8 weeks (after each radiological evaluation) |       |       |       |       |       |       |       |                        | X                                       |                            |
| 7.10             | Follow-up                                  |                                                               |                                                                                  |        |       |                                                    |       |       |       |       |       |       |       |                        |                                         |                            |
|                  | Follow-up visits                           |                                                               |                                                                                  |        |       |                                                    |       |       |       |       |       |       |       |                        |                                         | Every 3 months until death |

Table 2: Schedule of activities

1. Documentation of *CDKN2A* mutation (chordoma cohort) and central diagnostic confirmation (STS, BS, and chordoma cohorts) is required for participation in the trial. For STS and BS cohort, a pre-screening test before screening is established, for the first CDK4 expression analysis done on already existing tumor block.
2. End-of-treatment evaluation must be done at the end of medication administration (within 4 weeks)
3. Baseline laboratory testing should be done within 7 days prior to initiation of treatment
4. Biochemistry: ALT, AST, total bilirubin, creatinine, alkaline phosphatase, glucose, albumin, total protein, LDH, chloride, phosphorus, sodium, potassium, calcium
5. Hematology: hematocrit, hemoglobin, leukocytes, red blood cells, neutrophils, platelets, RDW
6. Women of reproductive age. The pregnancy test should be done before starting treatment (within 7 days prior to inclusion) and then every 3 cycles until the end of treatment
7. In addition to other physical examinations (see section 7.6), weight and height are required at baseline, and height is not required on day 1 of each cycle
8. ECG within 14 days prior to enrollment
9. Preferably CT scan
10. FDG-PET, MRI diffusion, bone scan (if indicated)
11. Medication is dispensed to the patient on the first day of each cycle
12. A biopsy in the baseline period (within 28 days before the start of treatment) will be necessary if there is no archive tumor specimen obtained in the 3 months prior (no systemic treatment must be present in this period) to the initiation of treatment
13. Blood collections: (1) Within 72 hours pre-treatment, (2) at the end of the first cycle (day 28), (3) after each radiological evaluation

